#### Sample size calculation

The sample size is based on patient participation in IBSM (primary outcome). We assume that one-third of the 15% to 20% of patients who have a written action plan
[9] are actually using it to conduct self-management activities. Assuming that with the MS, 5% of the patients are frequently using the IBSM to monitor their asthma, we will consider the IS and ES successful if an increase of 25% is achieved (alpha 0.05 and beta 0.20). Using a correction for clustering of patients in practice (intra-cluster correlation coefficient: 0.25), we calculated that we need 10 patients in each of 42 practices 14 practices in the MS, IS, and ES, respectively to be invited to participate in IBSM using PatientCoach. This gives a total of 420 patients.

#### IBSM support program

The IBSM support program consists of both a generic web-based system and an instruction visit for patients.

#### PatientCoach

Patientcoach.nl is a generic web-based system that supports self-management of patients with a chronic condition. It includes modules for coaching, personalized information (*i.e.*, inhalation technique), self-monitoring, reminders, treatment plan, (motivational) feedback, e-consultations and a forum. PatientCoach has been developed by the Leiden University Medical Centre (LUMC)
[16]. The program includes options for weekly assessment of the level of asthma control
[28,29] and a quarterly-assessment of asthma-related quality of life
[30]. Furthermore, it offers tools for professionals and patients, to help them to incorporate IBSM respectively into routine asthma care and daily life, such as: reminder options for home monitoring by ACQ and lung function; reminder options for routine consultations (*i.e.*, digital agenda); reminder options (*i.e.*, a general agenda) for regional educative sessions on asthma, *i.e.*, hosted by the patient association of the Netherlands Asthma association; and a forum for professionals.

PatientCoach contains a research module that consists of electronic versions of questionnaires for assessment of quality of life
[31], health education impact
[31], self-reported medication adherence
[32], illness perceptions
[33] and costs
[34].

#### Self-management support session for patients on PatientCoach

Patients participating in PatientCoach will be supported by their PN and/or GP. PNs will be asked to invite the patient for at least one consultation (double-consultation) that aims to inform patients on how to use PatientCoach, particularly focusing the essential self-management skills in asthma (*i.e.*, monitoring, inhalation technique).

#### Usual care

PNs in all strategies will be asked to conduct follow-up on patients in concordance with the Dutch guideline for general practice on asthma in adults, which recommends a medical review and treatment adjustment every two to four weeks in unstable asthma and medical review once or twice a year for patients whose asthma is not under control
[35]. The guideline states that routine asthma consultations include assessment of asthma control, medication, adverse events, adherence, and measurement of lung function. The guideline is concordant with current international guidelines, such as the Global Initiative for Asthma guideline
[1].

#### Implementation strategies

The implementation period is divided in a start-up and an execution phase (Tables 
2 and
3).

**Table 2 T2:** Overview of implementation strategies

	**Implementation strategy***		
	**MS**	**IS**	**ES**
**Start-up phase**			
**Practice recruitment**			
Recruitment letter	X	X	X
Reminder (letter)	X	X	X
Reminder (telephone)		X	X
**PatientCoach information**			
Manual	X	X	X
Information session	X	X	X
On site instruction		X	X
Workshop professionals	X	X	X
**Patient recruitment**			
By general practice	X	X	X
On site support (patient selection/invitation)	X	X	X

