**Execution phase**			
**Continuing support**			
Follow-up by the practice coach team			X
Outreach visit (if necessary)			X
Workshop professionals (implementation issues)			X

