### Minimum strategy (MS)

#### Start-up phase basic components

Practice recruitment: practices receive an information letter on IBSM support by using PatientCoach. Practices will receive a reminder letter within four weeks.

Participating physicians will be asked whether their non-responding colleagues in their practices would be interested in participation. On meetings for professional groups and patient organisations PatientCoach team members will present information on self-management and web-based support.

Patient recruitment: GPs are asked to invite at least ten patients to use PatientCoach.

PatientCoach information session for participating practices: In addition to a general announcement, professionals receive a manual on PatientCoach. Professionals (GP and/or PN) have the opportunity to join a PatientCoach information session. This information session is focused on the principles and usage of the IBSM program by the PN and patients, including home measurement of lung function as forced expiratory volume in one second (FEV_1_) using an electronic hand-held spirometer (PiKo-1: Ferraris; Hertford, UK). Finally, a short on-site training in usage of the PatientCoach system focusing on integration within the local primary care information system is offered to practices.

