#### Intermediate strategy (IS)

This includes a start-up support package that is additional to the components of the MS in the start-up phase. During the execution phase the IS does not differ from the MS.

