#### Start-up support package

The start-up support intermediate package consists of: Practice recruitment. General practices receive an invitation letter that includes all components of the Start-up Support Implementation strategy. Non-responding practices receive a reminder letter within four weeks and if necessary, practices are phoned.

On-site support for patient recruitment. PatientCoach team members offer practices the opportunity to make a patient selection in the patient registries of participating GPs.

PatientCoach start-up training. PNs and GPs are invited for an interactive session (duration: two hours) with colleagues. In this session, professionals are stimulated to discuss with each other on how to apply IBSM in their own practice. This training is focused on a proactive attitude toward patients and supporting them in their self-management skills by using IBSM support:

1. Exploration of a patient’s knowledge about asthma, illness perceptions
[36,37], and the ability to integrate (internet-based) self-management activities into their daily life; *i.e.*, by exploring difficulties and discussing solutions.

2. Asthma control: assessment of the level of asthma control; patients are invited to discuss their most recent ACQ-score. Reasons for poor asthma control in patients are discussed, and the subsequent management strategy will be discussed.

3. Medication: information on side-effects; instruction, exploration of therapy adherence, and checking correct inhaler technique.

4. Asthma related lifestyle: smoking cessation, avoidance of triggers, regular exercise;

5. Asking about and treating rhinitis, which is known to influences asthma outcomes
[38].

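### Table 2 and the sentence after Table 3 give the minimum strategy the professional workshop and patient-selection support that the text defines as the intermediate strategy's additions

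*Protocol article*

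**What the plan says.** **Definitions.** The Abstract, the list of strategies in the Background and the interventions row of Table 1 agree. MS is distribution of the programme only. IS is MS plus help in selecting patients and training for professionals. ES adds further training and continuing support.

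**IS text.** The Intermediate strategy section describes a "start-up support package that is additional to the components of the MS" during start-up, and says that IS and MS are the same in the execution phase. The package contains telephone contact with non-responding practices where needed, on-site selection support ("PatientCoach team members offer practices the opportunity to make a patient selection") and a two-hour interactive training session.

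**MS text.** The Minimum strategy section lists letters, a manual, an optional information session and "a short on-site training in usage of the PatientCoach system". GPs are asked to invite patients themselves. Neither selection support nor the interactive session appears.

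**Table 2.** The start-up row "Workshop professionals" and the row "On site support (patient selection/invitation" are marked for MS, IS and ES. The rows "Reminder (telephone" and "On site instruction" are blank for MS.

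**Sentence after Table 3.** It says that all strategies have professional-directed components and gives professional training and help with patient selection as the examples.

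**The concern.** The Hypotheses section sets the tailored strategies (IS and ES) against a non-tailored MS. Because IS and MS do not differ in the execution phase, the whole IS–MS contrast rests on the start-up components. Table 2 and the sentence after Table 3 place the two components that define IS in the comparator arm.

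If MS practices were supported in that way, a small IS–MS difference could mean that start-up support does not work, or only that both arms had it. The Implications section asks whether a focus on the start-up period alone is sufficient, and the trial could not answer that.

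**Working it through.** **1. Rows against text (start-up phase)**

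| Component | Table 2, MS | MS section | IS definition and section |
|---|---|---|---|
| "Workshop professionals" | marked | not listed | training is an IS addition |
| "On site support (patient selection/invitation" | marked | not listed; GPs invite | selection support is an IS addition |
| "On site instruction" | blank | a short on-site system training is offered | not named in the IS package |
| "Reminder (telephone" | blank | reminder letter only | telephone contact if necessary |

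The first two rows contradict the text. The workshop row cannot be the information session, which has its own row marked for all arms, nor the execution-phase workshop, which has a separate ES-only row. The two-hour IS training is the remaining match. The third row probably conflicts, but the table does not define it. The fourth agrees with the text.

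**2. What still separates the arms if Table 2 is read literally**

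- IS against MS: 2 rows (telephone reminder, on-site instruction). It is 1 row if the on-site training offered to MS is the same thing as on-site instruction.
- ES against IS: 3 execution-phase rows ("Follow-up by the practice coach team", outreach visit, second workshop).
- ES against MS: 2 + 3 = 5 rows (or 1 + 3 = 4).

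**3. Is the table merely broken in conversion from PDF?** Unlikely. Neighbouring rows keep their blank MS cells, and the sentence after Table 3 says the same in prose.

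**4. The plan's sample size.** Inputs from the Sample size calculation section: MS 5%, an increase of 25% (read as percentage points, so 30%), alpha 0.05, power 80%, ICC 0.25, 10 patients per practice. Two-sided testing is assumed, because the section does not say.

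- Design effect = 1 + (10 − 1) × 0.25 = 3.25.
- Two-proportion formula with continuity correction: 43 per arm. 43 × 3.25 = 139.75, hence 14 practices and 140 patients per arm, 420 in total. The plan's figure is reproduced. (The uncorrected formula at two-sided 0.025 also gives 43.)

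This figure does not depend on Table 2.

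**5. Illustration of dilution.** Effective size per arm n = 140 / 3.25 = 43.08. With IS held at p2 = 0.30, MS at p1 and p̄ their mean, the uncorrected two-sided 0.05 formula is

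Power = Φ{ [ (p2 − p1)√n − 1.96 √(2p̄(1 − p̄)) ] / √[ p1(1 − p1) + p2(1 − p2) ] }.

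At p1 = 0.05: (0.25 × 6.563 − 1.96 × 0.5374) / 0.5074 = 1.158, so power is 88%.

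| MS rate | Status | Power |
|---|---|---|
| 5% | plan's assumption | 88% |
| 10% | assumed | 65% |
| 15% | assumed | 38% |
| 20% | assumed | 19% |

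The series starts at 88% and not 80% because it uses the uncorrected formula throughout. Only the decline should be read from it.

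**The case against.** The strongest defence is that the narrative preserves the intended contrast. Three statements of the definitions and the detailed strategy sections agree with each other. Table 2 is captioned only as an overview, and nothing says that the team delivers from it. Misplaced marks are therefore at least as plausible as a contaminated MS arm. Attendance at training and professionals' adherence to the strategy are also to be registered, so workshop attendance by MS practices could be seen.

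Much of this stands. The article does not show that MS practices have received, or will receive, these components. But the prose is itself split, because the sentence after Table 3 sides with the table, and nothing states which version governs. Registering attendance would help to detect the problem afterwards; it does not settle what MS is meant to contain.

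Three stronger readings are tempting and are not supported:

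- **That the contrast disappears.** Table 2 still separates IS from MS on the telephone reminder and on-site instruction.
- **That ES against MS would test execution-phase coaching only.** ES also has those two start-up rows, which MS lacks in the table.
- **That a specific power loss can be quoted.** Halving the contrast (MS at 17.5%) would give 27%, but the documents give no participation rate for an MS arm with this support.

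**Conclusion.** The contradiction is real and concerns the content of the comparator arm. Two start-up components clearly conflict, and a third, on-site instruction, probably does. If MS were delivered as Table 2 prints it, it would receive both elements that define IS, and the IS–MS comparison would lose most of its intended content. ES–MS would be weakened but would keep five differing rows, or four if on-site instruction is common to both arms.

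The direction of bias, toward null, assumes that training and selection support do raise participation. Its size cannot be derived from the documents. The range of 88% down to 19% shows only how sensitive the comparison is to a rise in the MS rate from 5% to 20% with IS fixed at 30%. Whether any dilution has occurred depends on what was delivered, which the article does not report.

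**What to change.** 1. Clear the MS cells in Table 2 for the start-up workshop and on-site patient selection, so that the table agrees with the Abstract, the Background list, Table 1 and the MS and IS sections.
2. Reword the sentence after Table 3 so that it no longer attributes professional training and selection support to all strategies. Correcting the table alone would leave this sentence in conflict.
3. Decide whether on-site instruction is part of MS, and make that row and the MS section agree.
4. State which description governs delivery and tell the delivery team.
5. Table 1 reports that patient recruitment is ongoing. Record, practice by practice, which of these components MS practices have already been offered or received, and take this into account when interpreting the IS–MS and ES–MS comparisons.

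The first four steps are corrections to a table and text and a notice to the delivery team. The fifth needs a short check of delivery records. The sample size calculation is unaffected.

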**PatientCoach tools**			
Reminders	X	X	X
**Execution phase**			
**Continuing support**			
Follow-up by the practice coach team			X
Outreach visit (if necessary)			X
Workshop professionals (implementation issues)			X
**Helpdesk**			
Technical issues (web-based/phone)	X	X	X
IBSM related issues (phone)	X	X	X

* MS = Minimum strategy; IS = Intermediate strategy; ES = extended strategy; IBSM = internet-based self-management support program (PatientCoach).

**Table 3 T3:** Study phases and time schedule

	**Planning (months)**
Start-up phase	6
- General practice recruitment/Instruction general practices	6
- Patient recruitment	
Execution phase	6
- Patient follow-up	
Follow-up per general practice (includes both start-up and execution phase period)	12

All strategies consist of patient-directed (*i.e.*, reminders for consultations), professional-directed (*i.e.*, training of professionals, support on patient selection), and organisational components (*i.e.*, helpdesk).

### Minimum strategy (MS)

#### Start-up phase basic components

Practice recruitment: practices receive an information letter on IBSM support by using PatientCoach. Practices will receive a reminder letter within four weeks.

Participating physicians will be asked whether their non-responding colleagues in their practices would be interested in participation. On meetings for professional groups and patient organisations PatientCoach team members will present information on self-management and web-based support.

Patient recruitment: GPs are asked to invite at least ten patients to use PatientCoach.

PatientCoach information session for participating practices: In addition to a general announcement, professionals receive a manual on PatientCoach. Professionals (GP and/or PN) have the opportunity to join a PatientCoach information session. This information session is focused on the principles and usage of the IBSM program by the PN and patients, including home measurement of lung function as forced expiratory volume in one second (FEV_1_) using an electronic hand-held spirometer (PiKo-1: Ferraris; Hertford, UK). Finally, a short on-site training in usage of the PatientCoach system focusing on integration within the local primary care information system is offered to practices.

#### Execution phase basic components

Practices have access to a web-based helpdesk for technical issues. For issues related to IBSM in asthma, professionals can consult the PatientCoach team by email and/or telephone.

#### Intermediate strategy (IS)

This includes a start-up support package that is additional to the components of the MS in the start-up phase. During the execution phase the IS does not differ from the MS.

#### Start-up support package

The start-up support intermediate package consists of: Practice recruitment. General practices receive an invitation letter that includes all components of the Start-up Support Implementation strategy. Non-responding practices receive a reminder letter within four weeks and if necessary, practices are phoned.

On-site support for patient recruitment. PatientCoach team members offer practices the opportunity to make a patient selection in the patient registries of participating GPs.

PatientCoach start-up training. PNs and GPs are invited for an interactive session (duration: two hours) with colleagues. In this session, professionals are stimulated to discuss with each other on how to apply IBSM in their own practice. This training is focused on a proactive attitude toward patients and supporting them in their self-management skills by using IBSM support:

1. Exploration of a patient’s knowledge about asthma, illness perceptions
[36,37], and the ability to integrate (internet-based) self-management activities into their daily life; *i.e.*, by exploring difficulties and discussing solutions.

2. Asthma control: assessment of the level of asthma control; patients are invited to discuss their most recent ACQ-score. Reasons for poor asthma control in patients are discussed, and the subsequent management strategy will be discussed.

3. Medication: information on side-effects; instruction, exploration of therapy adherence, and checking correct inhaler technique.

4. Asthma related lifestyle: smoking cessation, avoidance of triggers, regular exercise;

5. Asking about and treating rhinitis, which is known to influences asthma outcomes
[38].

#### Extended strategy (ES)

The ES does not differ from the IS during the start-up phase. However, this strategy includes a patient coach package that is additional to the components of the MS/IS during the execution phase.

### Execution phase

#### Practice coach package

The practice coach package consists of the following components:Ongoing support: follow-up by PatientCoach team members at one, three, and five months after baseline by email, telephone, or face-to-face. During these planned consultations, members of the PatientCoach team will explore whether practices experience difficulties. Solutions and future recommendations are given. An outreach visit
[23,39], both PatientCoach team initiated (planned) or professional initiated (unplanned), will be conducted when necessary.

Interactive session with professionals: within three months after starting to use PatientCoach, professionals will have the opportunity to participate in an interactive session with colleagues. This session will be focused on identifying problems for PatientCoach implementation, and solutions will be discussed.

#### Measurements and outcomes

Primary outcome measures are the proportion of referred patients that participate in IBSM and the proportion of patients that have clinically relevant improvement in the asthma-related quality of life as measured by the Asthma Quality of Life Questionnaire
[30]. Patient usage of IBSM is based on monitoring of the level of asthma control using the Asthma Control Questionnaire
[28,29]; monitoring of ACQ during two out of three months ACQ-monitoring compliance.

#### Patient level

Demographic characteristics (*i.e.*, educational level, atopy, smoking status, and symptom-free days) are obtained at baseline (Table 
4). The effect evaluation includes clinical outcomes (asthma control, lung function, usage of airway treatment, and the presence of exacerbations) and self-management related outcomes (health education impact, self-reported medication adherence and illness perceptions) and patient utilities (asthma symptom utilities).

**Table 4 T4:** Outcome measures

	**0 Months**	**3 Months**	**6 months / end-point**
**Demographic characteristics**	A		N
**Clinical**			
Asthma control (ACQ)	A	A,N	
Lung function (FEV_1_) []	A	A	A
**Quality of life/patient utilities**			
Asthma related quality of life (AQLQ)	A	A	A,N
Utilities: (EQ-5D)	X	X	A,N
**Self-management**			
Education (HeiQ)	X		X, N
Medication adherence (MARS)	X	X	X
Illness perceptions (B-IPQ)	X		X
**Costs**			
Healthcare and other costs (CostQ)	X	X	X, N

A = all strategies; X = Intermediate and Extended strategy; N = non-participating practices.

Asthma control is using the 7-item Asthma Control Questionnaire (ACQ), the optimal cut-point for ‘controlled’ is ≤0.75 and a value of ≥1.50 confirms ‘not controlled’ asthma
[28]. Lung function will be measured as the Forced Expiratory Volume in one second (FEV_1_). Patients receive a handheld electronic spirometer (PiKo-1: Ferraris; Hertford, UK) and are instructed to report the highest value of three measurements in the morning before taking medication
[1]. The presence of exacerbations is assessed; they are defined as deterioration in asthma that required emergency treatment or hospitalization (collected by quarterly questionnaire) or the need for oral steroids for three days or more (collected by pharmacy records) or the need for oral steroids for asthma as judged by the attending physician.

Exacerbations are defined according to ATS/ERS statement
[40]:

Severe exacerbations require at least one of the following: systemic corticosteroids (tablets, suspension, or injection) usage or an increase from a stable maintenance dose, for three or more days; or a hospitalization or emergency room visit because requiring systemic corticosteroids.

Moderate exacerbations require ≥ 1 of the following features, lasting for two or more days: deterioration in symptoms, deterioration in lung function, and/or increased rescue bronchodilator use.”

Health education impact is assessed by the health education impact questionnaire (heiQ)
[41]. Self-reported medication adherence is measured by the Medication Adherence Report Scale
[32]. Illness perceptions are assessed by using the Brief Illness Perception Questionnaire (Brief IPQ)
[33]. In addition, asthma symptom utilities are obtained from the Asthma Quality of Life Questionaire (AQLQ)
[42], EQ-5D
[31,43] and a visual analogue scale (VAS).

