## Methods

### Study design

This study is a three-arm, cluster randomized trial with a cluster pre-randomisation design
[7] (Figure 
1). Because the implementation strategies are primarily targeted at general practices, randomisation will occur at practice level (CONSORT guidelines for cluster trials, Table 
1[27]). Prior to obtaining informed consent from GPs and patients, practices will be allocated to one of the strategies. Follow-up per practice is 12 months. At patient level, follow-up duration is six months. In the ES and IS strategies, individual patient outcomes will be evaluated at baseline (first visit of a patient to the general practice for instruction on IBSM), and three and six months after a patient’s start with IBSM. Individual patient outcomes in the MS strategy will be evaluated at six months (end-point evaluation) after a patient’s start with IBSM.

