#### Patients

General practices will be asked to invite at least ten 10 patients per practice to participate in IBSM. Based on previous studies on asthma within general practice, we know this is feasible
[16]. Those patients not willing to participate in IBSM will be asked informed consent to participate in an endpoint evaluation at six months. Informed consent will be obtained during a consultation with a patient’s PN or GP.

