#### Endpoint evaluation

Patients in practices randomized to the MS strategy, and those patients in the IS and ES strategy not willing to participate in IBSM support, will only be approached for an endpoint evaluation at six months after their start with PatientCoach.

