#### Analysis

The analysis is carried out on an intention-to-treat basis*.* Analyses include descriptive statistics and comparisons on process and effect evaluation. Differences are compared between implementation strategies using a random-effects analysis accounting for within-patient repeated measurements and clustering on general practice, or nonparametric comparisons, such as chi-square, as appropriate. All data are analyzed using STATA.

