## Discussion

This study is designed to investigate the effectiveness and cost effectiveness of implementing IBSM by comparing three different implementation strategies (MS, IS, and ES) in a three-arm cluster-randomized trial with a cluster pre-randomization design. The IBSM application contains functionalities that are characterized by some innovative aspects, such as options for e-consultation and integration of results into the general practice system. These functionalities address previously stated requirements for both patients and professionals. The findings of this study will lead to recommendations for a potential cost-effective strategy that can be used for the implementation of IBSM in practice.

This study has been designed for translation of research findings into actual practice. Primarily, the pre-cluster randomization design allows us to study the effect of the different implementation strategies on the number of primary care practices that participate in IBSM. Second, the impact of the different strategies at both professional and patient level on actual implementation (*i.e.*, participation, patient outcomes, and cost-effectiveness). Third, general practices are given a leading role to adapt and internalize IBSM in clinical practice: the project team will only act as facilitators to these practices. Additionally, the influence of research activities on implementation has been incorporated in the design of this study, because these might function as an extra stimulus for both practices and patients to adapt and internalize IBSM during the study period. Therefore, the content of the MS strategy is not only similar to commonly used (non-tailored) implementation strategies, but also the number and amount of research activities are minimized. This is in contrast to the IS and ES strategies, which are specifically designed to address previous identified barriers. These differences give us the opportunity to study how much support is required by general practices for IBSM implementation. Finally, this study evaluates the costs of the implementation from a societal perspective, which is in contrast to other implementation studies
[18,48]. Therefore, we will include costs for asthma care from both non-participating practices and non-participating patients.

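### Patients who decline IBSM in the IS and ES arms have no baseline AQLQ, so the quality-of-life primary outcome can be computed there only for acceptors

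*Protocol article*

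**What the plan says.** The protocol article treats patients who decline IBSM in several places.

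- **Patients:** "Those patients not willing to participate in IBSM will be asked informed consent to participate in an endpoint evaluation at six months". Consent is taken at a consultation with the practice nurse or GP.
- **Endpoint evaluation:** alongside the minimum strategy (MS) patients, "those patients in the IS and ES strategy not willing to participate in IBSM support" are a group that "will only be approached for an endpoint evaluation at six months after their start with PatientCoach".
- **Study design:** in IS and ES, "individual patient outcomes will be evaluated at baseline (first visit of a patient to the general practice for instruction on IBSM"), then at three and six months.
- **Measurements and outcomes; Analysis of clinical data:** one of the two primary outcomes is the share of patients whose AQLQ improves by a clinically relevant amount, set at 0.5.
- **Analysis:** "The analysis is carried out on an intention-to-treat" basis.
- **Table 4, AQLQ row:** A at 0 months, A at 3 months, and A,N at six months/end-point. The legend reads "A = all strategies; X = Intermediate and Extended strategy; N = non-participating practices".
- **Discussion:** "we will include costs for asthma care from both non-participating practices and non-participating patients", which treats these as two groups.

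**The concern.** A responder outcome based on change needs two values per patient. The schedule gives decliners one. What can be computed in IS and ES is therefore the proportion improved among those who accepted IBSM, not among those invited.

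Acceptance happens after randomisation. It is what the strategies are built to influence, and it is closely tied to the other primary outcome, patient participation. Comparing arms among acceptors compares groups that the allocated strategy helped to select, so the protection of randomisation is lost for this outcome. Missing baselines also cannot be recovered later by any analysis plan.

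**Working it through.** **1. Denominator.** The Sample size calculation section gives 14 practices × 10 patients = 140 invited per arm, and 3 × 140 = 420 in total. The figure reproduces: comparing 5% with 30% (5% plus 25 points), two-sided, alpha 0.05, power 80%, with continuity correction, needs 43 per arm. The design effect is 1 + (10 − 1) × 0.25 = 3.25, and 43 × 3.25 = 139.75, rounded up to 140. This only fixes the denominator and says nothing about the schedule.

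**2. Which AQLQ values each IS/ES patient has.**

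| Group | 0 months | 6 months | Change computable? |
|---|---|---|---|
| Accepts IBSM | Yes, at the instruction visit | Yes | Yes |
| Declines IBSM, consents to endpoint evaluation | No: endpoint only, and no instruction visit | Yes | No |
| Declines both | No | No | No |

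Reading N in Table 4 as decliners changes nothing, because N stands in the AQLQ row only at end-point.

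**3. Number without a change score.** With acceptance *a*, this is 140 × (1 − *a*). The protocol gives no acceptance rate, so *a* is an assumption.

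- *a* = 30%: 140 × 0.70 = 98
- *a* = 50%: 140 × 0.50 = 70
- *a* = 70%: 140 × 0.30 = 42

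**4. Effect on the estimate.** The proportion improved among all invited is *a* × p(acceptors) + (1 − *a*) × p(decliners). Since p(decliners) is unobserved and may lie anywhere from 0 to 100%, the invited-population proportion is uncertain over a span of (1 − *a*): 70, 50 or 30 percentage points at the three acceptance levels.

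Illustration with assumed rates of 50% improving among acceptors and 20% among decliners:

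- *a* = 30%: 0.30 × 50% + 0.70 × 20% = 29%
- *a* = 70%: 0.70 × 50% + 0.30 × 20% = 41%

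Acceptors alone show 50% in both cases. Two arms that differ by 12 points (41% − 29%) over all invited patients would appear identical.

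**5. Time origin.** The six-month evaluation is timed from starting PatientCoach. A decliner never starts, so the date of that evaluation is undefined.

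**The case against.** **Is the legend just a slip?** Very possibly: N follows the endpoint-only pattern that the text gives to decliners. The legend is a secondary inconsistency, and the missing baseline rests on the Study design and Endpoint evaluation sections. A reader might infer from the legend that decliners have no scheduled assessment at all. The documents do not support that, because the Patients and Endpoint evaluation sections both give them a six-month evaluation.

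**Could the analysis plan settle it?** The outcome definition names no denominator, and a plan that is not shown might count patients without a change score as not improved. That yields a number but not the missing information. With the assumed rates above, it gives 0.30 × 50% = 15% and 0.70 × 50% = 35%, a gap of 20 points where the true gap is 12. The outcome would then partly re-measure participation.

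**Is the question about users only?** The Objectives ask separately whether IBSM improves quality of life, which can be read that way. If so, the intention-to-treat statement does not fit that outcome, and a between-arm comparison among users is not a randomised one.

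**Are the figures too strong?** The 30% is the design's target for frequent use, not an acceptance rate. Acceptance is at least as high as use, so if the target is met, 98 is the upper end. A reader might also infer that a strategy recruiting fewer, keener patients will show a higher responder proportion. That is possible in principle, but neither the documents nor the illustration shows it. The illustration shows only that an acceptors-only result does not respond to acceptance.

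**Is the MS arm the larger problem?** The text gives MS patients the six-month evaluation only, while Table 4 codes their AQLQ at 0 and 3 months. If the text governs, improvement cannot be computed in the comparator arm at all. That objection stands, but it is a separate contradiction: a baseline in MS would still leave IS and ES decliners without one.

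**Conclusion.** The point holds. As scheduled, the quality-of-life primary outcome in IS and ES can be computed only for patients who accept IBSM. This conflicts with the stated intention-to-treat analysis and conditions on a post-randomisation variable that the strategies aim to change.

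The conclusion rests on reading the Endpoint evaluation section literally (endpoint only) together with the definition of baseline as the instruction visit. It needs no assumption about rates. Its size does: between 42 and 98 of 140 invited patients per arm for acceptance between 70% and 30%. The direction and amount of any bias between arms cannot be determined from the protocol.

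**What to change.** 1. Collect the AQLQ from consenting decliners at the consultation where consent to the endpoint evaluation is taken.
2. Use that consultation date as the origin for their six-month evaluation.
3. Analyse the responder outcome over all consenting invited patients, and report per arm how many invited patients refused consent.
4. Give non-participating patients their own code in Table 4, separate from non-participating practices, and state which items each group supplies. This brings the table into line with the Patients, Endpoint evaluation and Discussion sections.
5. Resolve the contradiction over the MS baseline between the text and code A in Table 4. Without that, no between-arm comparison of improvement is possible, whatever is done for decliners.

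The cost is one questionnaire at a contact that already takes place, plus corrections to the text and table. The downside is slight extra burden and some refusals. Patients who refuse consent remain missing, so the change reduces the selection problem without removing it. Table 1 reports that patient recruitment is under way, so decliners already seen cannot be given a baseline retrospectively, and the change should be made promptly.
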